### Procalcitonin-guided decision making

The normal age-adapted PCT ranges according to our previous study are shown in Figure 1. To provide a margin of safety, the maximal normal value of PCT is defined as 10 ng/ml (18-36 hours of life) which, according to the literature is about 50% of the highest PCT concentrations measured in neonates with respiratory distress not related to infection [33].

**Figure 1 F1:**
[figure not shown]
**Normal age-adapted PCT ranges. Grey boxes = age-adapted normal range **[47].

At time-point T = 24-72 h (one time-point between 24-72 h after start of antibiotic therapy: time-point of positive culture result or time-point of early stop of antibiotic therapy (less than 72 h of therapy) or 72 h after start of therapy) neonates will be assessed and divided into categories of risk classification (Table 1 and 2): infection proven (category 1), infection probable (category 2), infection possible (category 3), and infection unlikely (category 4). The treating physician will decide in which risk classification a neonate belongs. Expected distribution based on the results of our first study [47]: Category 1 50%, Category 2 30-35%, Category 3 and 4 15-20%.

**Table 1 T1:** Risk of infection classification categories

Category 4: Low risk (Infection unlikely)	**One **abnormal finding:
	- pre/perinatal risk factor*, OR
	- suspect clinical symptom*, OR
	- abnormal laboratory examination*
**Category 3:** **Intermediate risk** (Infection possible)	**Two **abnormal findings:
	- pre/perinatal risk factors*, AND/OR
	- suspect clinical symptoms*, AND/OR
	- abnormal laboratory examinations*

**Category 2:** **High risk** (Infection probable)	**Three **abnormal findings:
	- pre/perinatal risk factors*, AND/OR
	- suspect clinical symptoms*, AND/OR
	- abnormal conventional laboratory examinations*

**Category 1:** **Proven infection**	≥ 1 abnormal finding (pre/perinatal risk factors, clinical symptoms, laboratory examinations) AND a **positive culture**

The assessment of risk of infection classification is independent of serum PCT levels.

* See assessment guidelines (Table 2)

**Table 2 T2:** Assessment guidelines

Pre/perinatal risk factors	Mother group B streptococcus (GBS) positive
	Maternal prolonged rupture of membranes (PROM) > 18 h
	Maternal chorioamnionitis (fever >38.5°, fetal tachycardia)
	Birth before 35 weeks of gestational age
**6 groups of suspect clinical signs and symptoms**	Respiratory distress/apnea
(signs and symptoms of one group = one abnormal finding)	Tachycardia/bradycardia
	Arterial hypotension/poor perfusion
	Hypothermia/hyperthermia
	Seizure/floppy infant/irritability/lethargy/poor feeding
	Vomiting/feeding intolerance/ileus

**Conventional laboratory examinations**	White blood cell count < 5 G/L
	CRP > 10 mg/L

The duration of antibiotic therapy in the standard group is based on the attending physician's assessment of the risk classification during hospitalisation: in category 4 patients, antibiotics are given for 2 - 3 days, in category 3 patients for 5 - 7 days. In the PCT group, if infection is considered to be unlikely or possible, antibiotic therapy is discontinued when two consecutive PCT values are within the normal range (Figure 1 Table 3). Antibiotic therapy can be continued despite fulfilled PCT criteria at the discretion of the attending physician. These diversions from the stopping rules will be reported for further analysis. If infection is proven (category 1) or considered to be probable (category 2) antibiotics are given for 7 - 21 days in both groups.

**Table 3 T3:** Duration of antibiotic therapy

	Standard group	PCT group
**Category 1 and 2**	7 - 21 days	7 - 21 days

**Category 3**	5 - 7 days	at least 24 hours, stop after 2 consecutively negative PCT-values

**Category 4**	36 - 72 hours	at least 24 hours, stop after 2 consecutively negative PCT-values

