## Background

Infections are the single largest cause of neonatal deaths globally [1]. Based on the onset, neonatal sepsis is classified into two major categories: early onset sepsis, which usually presents with respiratory distress within 72 hours of age and late onset sepsis that usually presents with septicemia after 72 hours of age. Sepsis in neonates is a significant contributor to morbidity and death, with mortality rates varying from 3% to as high as 50% in some series, especially with gram-negative pathogens [2-6]. The incidence of early-onset sepsis in term neonates in The Netherlands 2003-2006 is approximately 0.6% [7].

Early diagnosis and treatment of the newborn infant with suspected sepsis are essential to prevent severe and life threatening complications. In contrast to the clear and valuable therapeutic options, the diagnosis of suspected early-onset neonatal sepsis is challenging. The early signs of sepsis in the newborn are non-specific. Therefore, many newborns with nonspecific symptoms undergo diagnostic studies and the initiation of treatment before the presence of sepsis has been proven. Blood culture is currently the gold standard for the diagnosis of sepsis. However, in addition to the fact that culture reports are available only after 48-72 hours, blood cultures are frequently false negative due to the small amount of blood that can be drawn from neonates [8]. The reliability of most laboratory markers, including white blood cell count (WBC), C-reactive protein (CRP), Procalcitonin (PCT) and IL-6 for the diagnosis of neonatal infection has been assessed in highly diverse groups of ill neonates with a mixture of diagnoses and conditions and has yielded variable results [9]. If culture results come back negative after 48-72 hours, the clinician has to decide whether to provide continued treatment.

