### Statistical analyses

This trial is designed to exclude a difference in the rates of re-infection or death greater than 2% (non-inferiority aspect of the trial). Assuming a 2% reinfection/death rate in each group, 770 patients are required per arm for a power of 80% at one-sided alpha of 0.025. Based on our data of the study in Lucerne [47], with this number of patients a difference between mean antibiotic therapy durations of 10 hours can be detected at two-sided alpha of 0.05 with a power of 95% (superiority aspect of the trial). To allow for some unevaluable cases 800 per group will be included.

Primary analyses: The two-sided 95% confidence interval for the difference (experimental - control) in re-infection/death rates will be calculated for the total randomized arms and if this difference excludes +2%, non-inferiority is considered to be shown [48]. Comparison of durations of antibiotic therapy will be done using the Mann-Whitney test with stratification by centre. Any patients dying will be considered as the worst outcome in this evaluation and their duration will be set at the highest duration found. All analyses will be done according to the intention-to-treat principle and will be done with stratification by centre. A per-protocol analysis, excluding patients with major protocol violations, will also be done.

Secondary analysis: Exploratory analysis of primary endpoints regarding the relations with and clinical outcomes assessed at T = 24-72 h will be done using logistic regression or Anova. In the Anova the duration's antibiotic treatment will be transformed logarithmically. All tests are two-sided and p = 0.05 is the limit of significance. These analyses will be informal only because it cannot be excluded that the ratings of clinical outcomes at T = 24-72 h are influenced by the PCT results in the PCT-group. In a secondary analysis reinfection/deaths rates will be compared between treatment arms using random effects logistic regression allowing for centre as a random factor.

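### Under the printed risk-category mix, the planned Mann-Whitney test of antibiotic duration has about 12-27% power, far below the superiority power the protocol claims

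*Protocol article*

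**What the plan says.** The section on procalcitonin-guided decision making gives the expected distribution over the four risk categories as "Category 1 50%, Category 2 30-35%, Category 3 and 4 15-20" per cent, and attributes it to the investigators' first, single-centre study. Category 1 requires a positive culture (Table 1).

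On treatment length the same section says: "If infection is proven (category 1) or considered to be probable (category 2) antibiotics are given for 7 - 21 days in both groups". For the standard arm it says: "in category 4 patients, antibiotics are given for 2 - 3 days, in category 3 patients for 5 - 7 days". In the PCT arm, categories 3 and 4 are treated for at least 24 hours and stop after two consecutive normal PCT values (Table 3).

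The Statistical analyses section, citing the same first study, says that with 770 infants per arm "a difference between mean antibiotic therapy durations of 10 hours can be detected at two-sided alpha of 0.05 with a power of 95" per cent. No SD is printed. The planned test is different in kind: "Comparison of durations of antibiotic therapy will be done using the Mann-Whitney test with stratification by centre". It is an intention-to-treat analysis of all randomised infants and is not limited to categories 3 and 4. The abstract says that power for superiority exceeds 80%.

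**The concern.** If 80-85% of infants are in categories managed identically in the two arms, any effect on duration must come from the other 15-20%. In the standard arm those infants already have the shortest courses, ending at or below the 7-day minimum of categories 1-2. Shortening them further changes their order only relative to one another, never relative to the large majority. A difference in means can register the hours saved; a rank test largely cannot.

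Duration of therapy is a co-primary outcome. Either a printed design input is wrong, or that outcome is severely underpowered for its named test.

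The mix looks doubtful on other grounds too. It expects half of all infants treated on suspicion to be culture-positive. The Background says that many newborns with nonspecific symptoms are treated before sepsis is proven, and that cultures often miss infection.

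The mix also determines what the 2-point safety margin means for the infants whose care actually changes.

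**Working it through.** **The plan's own figures**

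- Non-inferiority: (1.960 + 0.842)² × 2 × 0.02 × 0.98 / 0.02² gives 770 per arm after rounding up. This reproduces the stated number.
- Superiority: no SD is given, so 95% cannot be reproduced directly. Solving for the SD that 95% power needs: 10 × √(770/2) / (1.960 + 1.645) = 10 × 19.62 / 3.605 = 54.4 h.

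**Power of the planned rank test under the printed mix**

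Let q be the share in categories 3-4, so q = 0.15 to 0.20. Assumptions:

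- q is the same in both arms and similar across centres.
- Category 1-2 durations have the same distribution in both arms and lie above those of categories 3-4.
- Best case for PCT: every PCT-arm category 3-4 course is shorter than every standard-arm one.

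Then P(PCT shorter) = 0.5(1−q)² + q(1−q) + q² = 0.5 + 0.5q².

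The null standard error is √(1541 / (12 × 770²)) = 0.0147, and z = 0.5q² / 0.0147.

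| q | P(PCT shorter) | z | Power, 770 per arm | Power, 800 per arm |
|---|---|---|---|---|
| 0.15 | 0.511 | 0.76 | 11.9% | 12.2% |
| 0.20 | 0.520 | 1.36 | 27.4% | 28.3% |

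Simulation (3,000 trials per scenario, 770 per arm, categories 3 and 4 equally frequent) agrees. Category 1-2 courses uniform over 7-21 days gave 12.0% and 27.4%; whole-day courses gave 12.2% and 27.7%. When the PCT-arm courses were instead spread over 24-72 h, so that separation was incomplete, power fell to 8% and 14%.

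**Ties**

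Ties among category 1-2 infants reduce the null variance by a factor of about 1 − (1−q)³. If every such course were exactly 7 days:

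- q = 0.15: z = 0.764 / √0.386 = 1.23, power 23%.
- q = 0.20: z = 1.359 / √0.488 = 1.95, power 49%.

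With 80% of those courses at 7 days and the rest at 10 days, simulated power was 16% and 35%.

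**Share needed**

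In the best case without ties, 80% power needs 0.5q² = 2.80 × 0.0147, so q is about 0.29. For 95% power, 0.5q² = 3.605 × 0.0147, so q is about 0.33. Both exceed the expected 15-20%.

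**The means statement**

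Take q = 0.15, categories 3 and 4 equally frequent, standard-arm averages of 144 h (category 3) and 54 h (category 4), and PCT-arm courses averaging 30 h. The overall mean difference is 0.15 × (99 − 30) = 10.4 h. With 80% of category 1-2 courses at 7 days and 20% at 10 days, the simulated SD is 53 h and a test on means has about 97% power. With courses uniform over 7-21 days the SD is 133-140 h, and the means test has about 33% (q = 0.15) to 49% (q = 0.20). So the 95% sentence depends on a spread that the article does not print.

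**Margin**

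If all excess events arise in categories 3-4, 2 points overall equals 0.02 / 0.20 = 10 to 0.02 / 0.15 = 13.3 points among those infants.

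**Reversed list (hypothesis)**

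With q = 0.80-0.85, P = 0.82-0.86, z exceeds 21 and power is essentially 100%. The margin then equals 0.02 / 0.85 = 2.4 to 0.02 / 0.80 = 2.5 points.

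The standard-arm duration for category 4 is given as 2-3 days in the text and 36-72 hours in Table 3. The two must be reconciled, but the best-case calculation does not depend on which applies.

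**The case against.** The strongest reply is that the 95% figure concerns means, not ranks. That stands. A reader might infer that the printed mix contradicts the 95% sentence. The documents do not support this: if category 1-2 courses cluster near 7-10 days, the mix can give both a difference of about 10 h and an SD near 54 h. What fails is carrying that figure over to the Mann-Whitney test.

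Second, 12-27% is not a hard ceiling. Heavy ties raise it, and so could unequal category shares between the arms. Table 1 says that classification is independent of PCT, but the Statistical analyses section concedes that ratings in the PCT arm may be influenced by PCT results. The article gives no size for this. Even total tying at 7 days leaves power near 50% or less.

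Third, a reader might conclude that the list is reversed. That would explain the low power and the surprising 50% culture-proven share, but the source study is not shown. The SD does not settle it: with 7-10 day courses the printed mix gives about 48-58 h and the reversed mix about 58-63 h, depending on assumptions.

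Fourth, it is tempting to set the 50% against the Background's statement that "The incidence of early-onset sepsis in term neonates in The Netherlands 2003-2006 is approximately 0.6" per cent. The denominators differ: that is a rate in term neonates generally, whereas the trial enrols infants already suspected of sepsis, from 34 weeks. It adds to the doubt but proves nothing.

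The margin conversion is secondary, and holds only if excess events are confined to categories 3-4.

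**Conclusion.** The concern holds as a conflict between the printed category mix and the rank test planned for a co-primary outcome. At 770 per arm, best-case power is about 12-27% with few ties, and about 20-50% if all category 1-2 courses are exactly 7 days. With incomplete separation within categories 3-4 and no heavy ties it is nearer 8-14%. All of these are far below the 95% in the statistical section and the more than 80% in the abstract. The result rests on equal category shares in both arms, a similar mix across centres, and the Table 3 durations.

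It does not show that the 10-hour means statement is arithmetically wrong, and it does not establish that the list is reversed. It shows that the mix, the test and the claimed superiority power cannot all stand together.

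**What to change.** 1. Check the expected distribution against the category table of the first study, and correct the sentence if it is misprinted.
2. State the SD behind the 10-hour, 95% figure.
3. Give superiority power for the centre-stratified Mann-Whitney test under the confirmed mix and the Table 3 durations, with the assumed spread and ties of category 1-2 courses.
4. If the printed mix is real, replace the 95% and >80% superiority figures with the power that the rank test has. Say also that, if excess events arise only in categories 3-4, the 2-point margin allows 10-13 points among those infants.

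If the mix is a misprint, the cost is one corrected sentence and one power calculation, with no change to enrolment. If it is real, correcting the text makes the plan honest but does not restore power. The superiority analysis would then need a design decision. Restricting the test to categories 3-4 is no simple way out, because classification happens after randomisation and may be influenced by PCT results.

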### Follow up

Patients with a recurrent infection will not enter the study for a second time. Recurrent infections will be analysed for focus and relapse of previous infection and will be treated at the physician's discretion. Recurrent infections in this trial will be defined as a new infection occurring within 72 hours after stopping antibiotic therapy for the initial infection. Any recurrent infection will be reported immediately to the steering committee.

Follow-up of the patients will be performed as in standard practice. Parents of discharged patients have 24 hours/day, 7 days/week access to the hospital and to contact a paediatrician on call. Phone numbers to contact the department will be provided upon discharge of the child. A follow-up interview after 1 month will be done with questions about undercurrent illness, physician visits, medications and hospitalisations.

### Adverse events

All serious adverse events will be reported to the principal investigator within 24 hours after their occurrence. Also the data and safety monitoring board and the ethical committee that approved the protocol will be informed by the principal investigator, according to the requirement of the ethical committee. All adverse events will be followed until they have abated, or until a stable situation has been reached. The members of the data and safety monitoring board will be blinded to the assigned intervention arm of the patient. At any time the members of this board can ask to be unblinded by requesting the treatment code from the independent statistical centre.

### Data collection and management

All data are collected in the neonatal intensive care department or pediatric ward. The medical history and used medication can be obtained from the patient's medical record. All collected data will be stored anonymously in the study database. Data management will be performed by the local investigator or the trial nurses of the participating center. The subjects will be identified by a trial identification number. Data base integrity and data safety as well as privacy are warranted by the participating research hospitals. Source data verification will be conducted by an independent Data Monitor.

An independent data- and safety monitoring committee is responsible for the ongoing conduct of the study, based on unbiased and independent review of efficacy and safety data. Dr. [name], paediatrician and clinical epidemiologist, Erasmus MC-Sophia, Rotterdam and Prof. [name], statistician at Erasmus MC will serve as members from The Netherlands and Prof. [name], neonatologist and head of the local ethical committee in Lucerne and Dr. [name], consultant neonatologist at the University Hospital in Zurich from Switzerland. The committee assesses the progress of the trial, and the safety data and advises whether to continue, modify or stop the trial every 3 months. The DMC charter informs about purpose, composition, responsibilities and structure of the committee. The board will operate under strict confidentiality.

### Ethical approval and trial registration

For this trial a nationwide ethical approval was requested for The Netherlands and local ethical approval was requested for all participating centres by their local ethical committee. Further participating study centers outside Switzerland and The Netherlands have to request approval by their ethical committee and to present the approval to the steering committee of the study. This trial will be conducted in accordance with the ethical guidelines of the World Medical Association's declaration of Helsinki Ethical Principles for Medical Research Involving Human Subjects as adopted by the 18th WMA General Assembly, Helsinki, Finland, June 1964, and amended by the 29th WMA General Assembly, Tokyo, Japan, October 1975; 35th WMA General Assembly, Venice, Italy, October 1983; 41st WMA General Assembly, Hong Kong, September 1989; 48th WMA General Assembly, Somerset West, Republic of South Africa, October 1996; 52nd WMA General Assembly, Edinburgh, Scotland, October 2000; 53th WMA General Assembly, Washington 2002 (Note of Clarification on paragraph 29 added); 55th WMA General Assembly, Tokyo 2004 (Note of Clarification on Paragraph 30 added); 59th WMA General Assembly, Seoul, October 2008. Also, this trial will comply with the regulations set forth by the Medical Research Involving Human Subjects Act (WMO) and other guidelines, regulations and Acts that apply.

This trial is registered in the U.S. National Institutes of Health's register, located at http://www.clinicaltrials.gov. under number NCT00854932.

## Discussion

It is essential for observational studies to compare new markers with the gold standard. The gold standard for the diagnosis of neonatal early-onset sepsis, i.e. a positive blood culture is often unreliable because of the frequent use of intrapartum antibiotics or insufficient amounts of blood available for culture [8]. Therefore, the problem of all observational studies of neonatal early-onset sepsis is the definition of sepsis. An intervention study offers a valuable alternative because the calculation of the main results is independent of the definition of sepsis. A control group is necessary to demonstrate that results from the intervention group differ from what will be observed in the standard group. We choose the design of a non-inferiority trial to show that a reduced duration of antibiotic therapy (superiority aspect) doesn't change the outcome (recurrence of infection, mortality).

As this trial will focus on the effectiveness and safety of a Procalcitonin-guided antibiotic treatment, it will not focus on the clinical reasons why a clinician will decide to start antibiotics. The start of antibiotic treatment is solely the decision of the attending neonatologist. The purpose of the choice to not interact with this clinical decision is to evaluate current clinical practice the closest without creating a bias towards biomarker started (or withheld) therapy. Therefore, when designing this intervention study, the definition of sepsis is less crucial than in an observation study, because in an intervention study all newborns are suspected to have bacterial infection and are therefore treated with antibiotics. The key point is the comparison of the outcomes after intervention. The probability of infection must be assessed by the attending physician at t = 24-72 h during the hospitalisation, because antibiotic treatment is not discontinued in neonates with proven or a high risk of infection based on maternal risk factors, clinical signs and symptoms, and conventional laboratory parameters.

Benefit of the study is a possible limitation of unnecessary use of antibiotics. On a population level, unnecessary long-term use of broad-spectrum antibiotics is a serious concern because it can promote the development of resistant bacteria, which will result in untreatable infections over time. Because the treatment consists of intravenously administered antibiotics, this means admission to the hospital for the neonate with separation of mother and child during these important first days of life. It is obvious that shortening this period when possible is desirable. It will also result in fewer painful punctures. Neonates need punctures for new intravenous lines very frequently, so shorter treatment will result in fewer punctures.

The burden of the trial is minimal, because only one extra time point for blood drawing will be done. For the other time points no additional diagnostic procedures are needed. The additional burden consists of a couple of extra blood drops during routine blood sampling.

The estimated risk is low. There is a low risk on discontinuing antibiotic treatment too early, resulting in the development of a neonatal infection with its morbidity and mortality. Based on follow-up data of our first study no mortality was observed in 121 neonates [47]. In only two children antibiotic treatment was restarted with good outcome and without proof for secondary infections due to early stop of primary antibiotic therapy.
